## Abstract

**Background:**

Osteoarthritis (OA) has long been considered as a degenerative disease of cartilage tissue resulting from bodily wear and tear. However, there is accumulating evidence that inflammation plays a key role in the pathogenesis of OA. In knee OA, the most common form of OA, exercise therapy as an effective component of early treatment addresses functional deficits, pain and inflammation. Since inflammation is critical for the development and progress of OA, anti-inflammatory therapies must be combined strategically.

In the course of the NUMOQUA project, an anti-inflammatory therapeutic diet named ‘Austrian Osteoarthritis Cuisine’ was developed. It is based on the framework of the New Nordic Diet combined with the food-based dietary guidelines of Austria, the guidelines for OA, the Austrian food culture and the principles of a sustainable diet. The present study examines the implementation of the ‘Austrian OA Cuisine’ combined with the evidence-based training programme GLA:D® (Good Life with osteoArthritis in Denmark) in Austrian patients with knee OA and the effects on quality of life, nutritional and inflammatory status, as well as oxidative stress parameters.

**Methods:**

A total of 60 participants aged 50 to 75 with knee OA will be included and randomly assigned either to the intervention group or the control group. All participants will undergo the GLA:D® programme in the first 6 weeks. Additionally, the intervention group will receive nutritional group training and individual nutritional counselling on the ‘Austrian OA Cuisine’ over 9 months. The control group will receive general information about a healthy lifestyle. Measurements at baseline and at 4 follow-up dates include nutritional, inflammatory and oxidative stress markers. Furthermore, anthropometric, behavioural and clinical data will be obtained. The recruitment process lasted from autumn 2022 to January 2024, followed by the intervention until October 2024.

**Discussion:**

The prevalence of OA is expected to increase in the future due to ongoing demographic changes and rising obesity rates. The expected results will provide important evidence on whether this interdisciplinary therapeutic approach could be a new, cost-effective and sustainable strategy to address the disease process of OA without negative side effects.

**Trial registration:**

ClinicalTrials.gov NCT05955300. Date of registration: 23rd of October 2023.

## Administrative information

Note: the numbers in curly brackets in this protocol refer to SPIRIT checklist item numbers. The order of the items has been modified to group similar items (see http://www.equator-network.org/reporting-guidelines/spirit-2013-statement-defining-standard-protocol-items-for-clinical-trials/).

## Introduction

### Background and rationale {6a}

Osteoarthritis (OA) is the most prevalent arthritic disease worldwide and is characterised by pain, effusion and stiffness leading to functional decline and loss of quality of life (QL) [1]. Furthermore, OA is the 11th highest global cause of disability resulting in significant morbidity and costs to the healthcare system [1, 2]. Developing lifestyle-based strategies to counteract clinical symptoms associated with OA is a high priority for biomedical research.

OA has long been considered as a degenerative disease of cartilage resulting from bodily wear and tear that affects the entire joint structure including the fibrillation and degradation of articular cartilage, thickening of the subchondral bone, formation of osteophytes and hypertrophy of the joint capsule. In addition to these structural pathologic changes in the joint, there is accumulating evidence that inflammation plays a key role in the pathogenesis of OA [3]. Triggered by tissue damage and metabolic dysfunction, inflammatory processes within the joint (local inflammation) may contribute to the development of chronic low-grade inflammation (systemic inflammation) [3, 4]. Factors that contribute to chronic low-grade inflammation include excessive energy intake, nutrient deficiency, obesity and abnormal metabolites [5]. Chronic low-grade inflammation, in turn, promotes local inflammation, which increases pain and effusion in the joint [4]. Together, local and chronic low-grade inflammation correlate with clinical symptoms of OA, accelerate the progression of the disease and might even influence its onset [4, 5].

Knee OA is the most common form of OA. Its prevalence rises with age and peaks at around 50 years of age, affecting more than 250 million people worldwide. The global prevalence of knee OA in 2010 was estimated to be 3.8% and it was higher in females than in males [6]. Between 1990 and 2019, the global prevalence of knee OA increased by 122% [7]. The medical costs caused by OA amount to approximately 1–2.5% of the national gross domestic product, while indirect costs associated with, e.g. work loss or premature retirement involves further financial burden [8]. Due to ongoing demographic changes, the prevalence of knee OA is expected to increase further in the future, which emphasises the magnitude of this disorder and stresses the need for a paradigm shift towards early and effective treatment [6]. For example, a recent study expects a 38% increase of OA in Austria from 2019 to 2080 [9].

Physical activity and exercise therapy represent important and effective components of early treatment and are therefore highly recommended as a first-line treatment of OA [10]. Despite strong evidence from more than 50 randomised controlled trials (RCTs) in knee OA and 10 RCTs in hip OA supporting the efficacy of exercise therapy, education and weight loss, the implementation of these modalities is still insufficient and suboptimal in clinical practice [11]. This may be due to the fact that there is a need for a comprehensive patient- and context-specific approach to successfully implement the clinical guideline [12]. Good Life with osteoArthritis in Denmark (GLA:D®) represents such an evidence-based treatment plan for knee and hip OA consisting of patient education and exercise therapy [13]. Studies have shown that GLA:D® is feasible and effective in reducing pain and improving function and QL, at least in the short term [12]. The GLA:D® training programme is offered and carried out exclusively by certified GLA:D® physiotherapists. Those instructors use GLA:D® in their usual care of OA patients in Austria.

While current exercise therapy programmes address pain and physical as well as functional deficits of OA patients, there is a need for more effective therapeutic strategies targeting chronic low-grade inflammatory processes [4]. The combination of exercise therapy and diet represents a promising approach to address this issue: firstly evidence shows that exercise provokes anti-inflammatory effects directly by inhibition of the inflammatory pathway and the production of inflammatory factors [14] and also indirectly by improving body composition through reducing abdominal adiposity [15]. Secondly, the diet composition exerts an important influence on inflammatory processes and plays a critical role in inflammation-related diseases [16, 17]. The combination of these two inflammation-modulating therapies might not only counteract the progression of OA but may possibly even prevent the onset of OA and improve function and QL in the long term.

A Western diet, characterised on the one hand by a high intake of fat, cholesterol, protein, sugar, salt, processed and ‘fast foods’ [18] - especially meat products - and, on the other hand, by a low amount of plant-based foods including fresh fruit and vegetables, legumes, seeds and nuts [19], evokes a state of chronic low-grade inflammation [16]. Therefore, lifestyle changes that positively influence inflammatory processes should be part of ‘first-line’ interventions in the management of OA, thereby reducing the rate of the disease’s progression, reducing weight and improving health by minimising a patient’s risk or manifestation of other lifestyle-related conditions [20].

Further, a plant-based therapeutic diet that elicits beneficial effects on the patients’ inflammatory and oxidative stress status helps to reduce pain and to improve the QL. It also offers the possibility to reduce non-steroidal, anti-inflammatory and analgesic medications [21]. This means that a therapeutic diet, which is a major part of adequate and comprehensive nutrition therapy, should focus on foods with high content of inflammation-modulating ingredients, like polyphenols and vitamins in fruit or vegetables, high-quality fatty acids in vegetable oils (rich in alpha-linolenic acid) and fish (rich in long-chain polyunsaturated n-3 fatty acids) [19, 21, 22] and a high intake of fibre [21]. Furthermore, probiotics [23] and fasting [24] can improve inflammation-associated symptoms too.

However, patients face several barriers while implementing a therapeutic diet [25] as part of nutrition therapy. Besides a ‘lack of willpower’ and limitations in time and money, dietary habits and taste preferences are mainly responsible for the adherence to a therapeutic diet [26, 27]. Therefore, recommendations to implement an anti-inflammatory therapeutic diet such as the Mediterranean diet [28, 29] in Austria might not be attractive for patients as it does not correspond with regional needs and habits [30]. Furthermore, it can be observed that dietary recommendations focus mainly on health aspects and less on environmental issues [31], although food (production) has a major environmental impact [32] which should be considered in prevention as well as in therapy [33]. These factors still remain unconsidered in the treatment of patients with OA. As a consequence, there is a need for a tasty and sustainable therapeutic diet for patients with OA.

For tackling these limitations, the New Nordic Diet (NND), which was developed in the early 2000s by experts in the fields of nutrition, gastronomy, environmental issues, food culture and sensory science, focuses on the principles of health, gastronomic potential and sustainability. The fundamental guidelines are as follows: first, more calories from plant-based foods and less from meat; secondly, more foods from the sea and the lakes; and third, more foods from the wild countryside. These principles and guidelines can be applied to any region [34] including Austria. Furthermore, the NND focuses on specific regional products, which is also a characteristic of the Austrian cuisine. Especially vegetables and fruits (e.g. roots, cabbage, legumes, apples, pears, or berries), cereals (e.g. whole grain rye, oats, or barley), lake fish and rapeseed oil [35] correspond highly with Austrian needs [36]. Finally, the SYSDIET study showed that the NND has anti-inflammatory characteristics [37, 38], which make the NND the perfect basis for the OA therapy.

To our knowledge, no study has examined the influence of NND on the symptoms, QL and progression of OA. Nor does a local adaptation of the NND exist in Austria. Implementing the NND as the tasty and sustainable therapeutic diet Austrian OA Cuisine would have several advantages over other dietary recommendations for patients with OA: stronger adherence to the therapeutic diet by taking regional preferences into account [39] and therefore

a better outcome in terms of a changed nutrition and inflammation status, a reduction of symptoms and increased joint function resulting in improved quality of life as well asa reduced environmental impact through the high amount of plant-based products, locally grown seasonal food and the high amount of organic products [40, 41]

With this research, we address the lack of knowledge concerning

the impact of exercise therapy AND nutrition therapy on the symptoms, QL and progression of knee OA as well asthe acceptance of the Austrian OA Cuisine in patients with knee OA as well as perceived social and cultural barriers [39] and supportive factors for the implementation.

### Objectives {7}

The main objectives of this study are, on the one hand, to analyse the effect of the nutrition therapy Austrian OA Cuisine combined with the GLA:D® training programme on QL in patients with mild to moderate knee OA. On the other hand, the study investigates the impact of a nutrition therapy combined with the GLA:D® training programme on symptoms, nutrition and inflammation status and oxidative stress markers, as well as joint function in patients with mild to moderate knee OA.

In particular, our main hypotheses are

H1: Austrian OA Cuisine combined with the GLA:D® training programme will improve QL in patients with mild to moderate knee OA.H2: Austrian OA Cuisine combined with the GLA:D® training programme will reduce symptoms in patients with mild to moderate knee OA.H3: Austrian OA Cuisine combined with the GLA:D® training programme will improve the nutrition status in patients with mild to moderate knee OA.H4: Austrian OA Cuisine combined with the GLA:D® training programme will improve the inflammation status in patients with mild to moderate knee OA.H5: Austrian OA Cuisine combined with the GLA:D® training programme will improve the oxidative stress markers in patients with mild to moderate knee OA.

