### Trial design {8}

This study is a parallel-group, two-arm superiority RCT to evaluate the impact of the nutrition therapy Austrian OA Cuisine combined with an evidence-based training programme (GLA:D®) in patients with mild to moderate knee OA in Lower Austria. The treatment combination of the nutrition therapy Austrian OA Cuisine and the GLA:D® training programme is compared with the treatment involving the GLA:D® training programme only.

Participants are informed about all aspects of the study and asked to sign a consent form. Participants are randomised at a 1:1 ratio (see {16a}). Staggered recruitment will be carried out to expand the recruitment phase and to handle all participants’ appointments and trainings more easily.

The duration of the intervention is 9 months. Within this intervention period, the intervention group undergoes the GLA:D® training programme for the first 6 weeks and receives the Austrian OA Cuisine for 9 months. The control group undergoes the GLA:D® training programme for 6 weeks and receives general information regarding a healthy lifestyle. During the 3 months follow-up phase, the intervention group members are expected to implement the Austrian OA Cuisine as well as the exercises of the GLA:D® training programme on their own into their daily life.

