### Interventions

#### Explanation for the choice of comparators {6b}

The research question was based on the PICO (Patient, Intervention, Comparison, Outcome) principle and reads as follows: The effects of the GLA:D® training programme combined with the nutrition therapy Austrian OA Cuisine - compared to the GLA:D® training programme alone - on quality of life in patients with knee osteoarthritis. To answer this research question, a randomised controlled clinical trial is conducted.

Both the intervention group and the control group participate in the GLA:D® training programme, which has already been shown to reduce pain and improve function as well as QL [15]. To examine the synergistic effects, the intervention group receives, in addition to the GLA:D® programme, training and counselling concerning the implementation of the developed nutrition therapy named Austrian OA Cuisine (see {11a}). The control group receives general information about a healthy lifestyle.

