## Statistical methods

### Statistical methods for primary and secondary outcomes {20a}

In this study, the focus is on the comparison of data collected at the beginning of the study (T0) and at the end of the study (T4; T0 + 12 months). For all statistical tests, the significance level is set at *p* < 0.05 in accordance with scientific standards. Data are analysed using IBM SPSS Statistics 28 or greater. Normal distribution of metric variables is tested with Shapiro–Wilk-Test and Q-Q-diagrams. For interpreting the results correctly, we also conduct a descriptive analysis showing the arithmetic mean and standard deviation of metric outcome parameters for each group. To control for outliers, we also report the minimum and maximum for each group in addition to a supportive graphical analysis. For interval and nominal scaled variables, we conduct a frequency analysis. To compare the effects of an evidence-based training programme (GLA:D®) with and without the nutrition therapy Austrian OA Cuisine, we conduct an analysis of variance (ANOVA) based on a mixed-linear model of repeated measures looking for assessing effects within each group (e.g. between baseline and the other data collection points) and between groups. In case variables are non-normal or non-metric in scale, we use the Friedman Test, respectively [83]. The group variable (intervention group or control group) serves as the independent variable and the observed outcome parameters (see {12}) serve as the dependent variable.

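### H1–H5 name no comparator and no test is named as deciding them, so a gain due to GLA:D alone could be read as confirming H1

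*Protocol article*

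**What the plan says.** The design is stated clearly. Trial design {8} says "This study is a parallel-group, two-arm superiority RCT", and that the combination "is compared with the treatment involving the GLA:D® training programme only". The research question under Explanation for the choice of comparators {6b} repeats this: the combination is to be judged "compared to the GLA:D® training programme alone", with quality of life as the outcome.

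The hypotheses in Objectives {7} do not carry the comparator over. H1 reads "Austrian OA Cuisine combined with the GLA:D® training programme will improve QL in patients with mild to moderate knee OA". H2 predicts fewer symptoms, and H3–H5 predict better nutrition status, inflammation status and oxidative stress markers, each time for the combination and with nothing to compare it to.

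Statistical methods {20a} sets out to compare GLA:D with and without the diet, makes group the independent variable, and puts the emphasis on T0 versus T4 (12 months). The repeated-measures analysis is described as "looking for assessing effects within each group (e.g. between baseline and the other data collection points) and between groups". Neither kind of effect is attached to a hypothesis.

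On GLA:D, which both arms receive, {6b} says that it is a programme "which has already been shown to reduce pain and improve function as well as QL". Background and rationale {6a} is more guarded: "feasible and effective in reducing pain and improving function and QL, at least in the short term". Section {6b} also gives a purpose for the design: "To examine the synergistic effects, the intervention group receives, in addition to the GLA:D® programme", the training and counselling on the diet.

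**The concern.** The randomised question is whether the diet adds something to GLA:D. H1–H5 ask a different question: whether patients given both improve. The plan will produce a test for each, the change from baseline in the intervention arm and the difference between arms, and it does not say which one settles the hypothesis.

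Read literally, H1 is met by a significant change in the intervention arm. That change contains whatever GLA:D does by itself, and regression to the mean and the passage of time as well. It therefore says nothing specific about the diet. At stake is whether a positive report on H1 would rest on the randomised comparison or on a before–after change.

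The synergy statement raises a related problem, since it promises a quantity that the two arms do not contain.

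**Working it through.** **Inputs.** From Sample size {14}: SD 15 and 25 participants per arm before drop-out. That section does not say whether 15 is the SD of a score or of a change; it is taken here as the SD at each visit. From {20a}: 5% significance level, T0 versus T4. Assumptions not in the documents: a common gain of 5, 8, 9 or 10 points in both arms at T4 (8–10 is the protocol's minimally important change, used here only as a scale), a diet effect of 0, a T0–T4 correlation ρ of 0.3, 0.5 or 0.7, and two-sided tests. The plan gives no figure of its own on this point to reproduce.

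**Step 1: SD of change.** SD_change = 15 × √(2(1 − ρ)), which gives 17.7 for ρ = 0.3, 15.0 for ρ = 0.5 and 11.6 for ρ = 0.7. The middle column below also applies if the protocol's 15 is meant as the SD of change.

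**Step 2: within-arm test.** This is a paired t-test on 25 participants with 24 degrees of freedom and noncentrality gain ÷ SD_change × √25. For a gain of 5 and ρ = 0.3, this is 5 ÷ 17.7 × 5 = 1.41. For a gain of 10 and ρ = 0.7, it is 10 ÷ 11.6 × 5 = 4.31. The probability of a significant change in the intervention arm is:

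| Common gain (points) | ρ = 0.3 | ρ = 0.5 | ρ = 0.7 |
|---|---|---|---|
| 5 | 27.2% | 35.9% | 54.2% |
| 8 | 58.0% | 72.5% | 91.0% |
| 9 | 68.2% | 82.1% | 96.0% |
| 10 | 77.1% | 89.2% | 98.5% |

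**Step 3: between-arm test.** Both arms have the same expected change, so the difference is 0 and the test should reject at its nominal level. A simulation of 20,000 trials with a common gain of 9 points and 25 per arm confirms it: 5.0%, 5.3% and 5.1% for ρ = 0.3, 0.5 and 0.7. In the same simulated trials the within-arm test was significant in 68%, 82% and 96%.

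**Step 4: synergy.** Write m(both), m(GLA:D), m(diet) and m(neither) for the mean outcome under each regimen. On the additive scale, synergy is [m(both) − m(GLA:D)] − [m(diet) − m(neither)]. The trial observes only m(both) and m(GLA:D). It can estimate the first bracket, which is the add-on effect of the diet. It has no information on the second.

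**The case against.** The intent is not in doubt. Sections {8} and {6b} name GLA:D alone as comparator, the sample size calculation refers to two groups, and {20a} includes between-group effects with group as the independent variable. On that reading H1 is shorthand for a between-arm statement, and the deciding contrast may be named in an analysis plan that is not shown. Synergy is mentioned once, and no hypothesis or analysis tests an interaction.

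Much of this stands. A reader might infer that a within-arm result would confirm H1, or that the plan has adopted a within-arm decision rule. The documents support neither: they state no decision rule, and they plan the between-arm test as well. A reader might also take the within-arm percentages as the trial's false-positive rate. They are not. If GLA:D works, the intervention arm really does improve and the within-arm test is right about its own null hypothesis. It misleads only when the result is credited to the diet. The size is also uncertain, because the documents give no GLA:D effect size and claim benefit at least in the short term, while the comparison in focus is at 12 months. Planning within-arm tests is not an error either.

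What remains does not depend on a missing detail. The published hypotheses differ from the published comparison, and no analysis plan could recover synergy from these two arms.

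**Conclusion.** The point holds as a mismatch between hypotheses and design. H1–H5 omit the comparator that the trial was built around, and the analysis section offers two kinds of test without tying either to them. A change from baseline in the intervention arm could therefore be read as confirming H1 when the diet adds nothing.

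Under the stated assumptions that reading would be available in 27% to 98.5% of trials with an ineffective diet, against about 5% for the between-arm test. The range is illustrative and is driven by the assumed common gain and correlation. The direction is firmer: any common gain that persists to T4 lifts the within-arm rate above 5% and leaves the between-arm rate where it is. The synergy statement cannot be met by this design, which identifies only the add-on effect. Neither issue undermines the randomised comparison itself.

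**What to change.** - Restate H1–H5 as superiority of Austrian OA Cuisine plus GLA:D over GLA:D alone on the outcome concerned.
- In {20a}, name the between-arm contrast in change from T0 to T4 (the group-by-time contrast) as the only test that decides these hypotheses.
- State that within-arm changes are supportive and are not evidence for the diet. They can still be tested and reported.
- In {6b}, replace the reference to synergy with the additional effect of the nutrition therapy on top of GLA:D.

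The cost is a revision of the text. No extra data, participants or visits are needed. The change is best recorded before the outcome data are analysed by arm.
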